### **6.4 Withdrawal of individual subjects**

Subjects can leave the study at any time for any reason if they wish to do so without any consequences. The principal investigator can decide to withdraw a subject from the study for urgent medical reasons.

#### **6.4.1 Specific criteria for withdrawal**

As before every surgery, the anaesthesiologist will evaluate the patient's health status when in Group A or when the patient has chosen for a definitive BAHA. In case the health status has worsened between inclusion and cochlear implant or BAHA surgery and the

anaesthesiologist advises not to continue, the patient will be excluded from further implantation.

### ***6.5 Replacement for individual subjects after withdrawal***

See also Section 4.4 Sample size calculation. To anticipate possible withdrawal 3 more subjects than needed according to the power calculation will be recruited in all groups. Therefore there will be no reason to replace subjects after withdrawal unless more subjects will withdraw than 3 per group.

### ***6.6 Follow up of subjects withdrawn from treatment***

During the study, each patient will stay in care of their own otorhinolaryngologist and audiologist, and subjects in group A also of their CI-team. In case a subject is withdrawn from the study he/she will continue with the standard medical treatment.

### ***6.7 Premature termination of the study***

Serious adverse events are not expected, but in case they do occur, each member of the research group has the right to terminate the study prematurely.

### ***6.8 End of study***

At the end of the study, all patients will be informed about the study outcomes. If this study shows CI is a superior treatment option for SSD, health insurance companies (Dutch: College voor Zorgverzekeraars [CvZ]) may change their reimbursement conditions. Patients from Groups B and C can opt for this new option via the ENT outpatient department. If this study shows BAHA or CROSS to be superior, reimbursement is already available in The Netherlands. They can also consult an ENT-specialist at the outpatient department for information on these treatment options. The procedure regarding their CI will be determined on an individual level.

## **7. SAFETY REPORTING**

### ***7.1 Section 10 WMO event***

In accordance to section 10, subsection 1 of the WMO, the investigator will inform the subjects and the reviewing accredited METC if anything occurs, on the basis of which it appears that the disadvantages of participation may be significantly greater than was foreseen in the research proposal. The study will be suspended pending further review by the accredited METC, except insofar as suspension would jeopardise the subjects' health. The investigator will take care that all subjects are kept informed.

## **7.2 Adverse and serious adverse events**

Adverse events (AEs) are defined as any undesirable experience occurring to a subject during a clinical trial, whether or not considered related to the investigational drug or intervention. All adverse events reported spontaneously by the subject or observed by the investigator or his staff will be recorded.

Besides the normal risks associated with surgery and general anaesthesia, AEs related to cochlear implantation or BAHA could be: implant failure, irritation, pain or infection and implant extrusion. Some specific AEs for cochlear implantation are complaints associated with electrical stimulation (i.e. tinnitus, facial nerve stimulation, dizziness) or uncomfortably loud sound sensation or no sound sensation due to failure of component parts.

A serious adverse event (SAE) is any untoward medical occurrence or effect that at any dose results in:

- death;
- is life threatening (at the time of the event);
- requires hospitalisation or prolongation of existing inpatients' hospitalisation;
- results in persistent or significant disability or incapacity;
- is a congenital anomaly or birth defect;
- is a new event of the trial likely to affect the safety of the subjects, such as an
- unexpected outcome of an adverse reaction, lack of efficacy of an investigational medicinal product used for the treatment of a life threatening disease, major safety finding from a newly completed animal study, etc.

All SAEs will be reported to the accredited METC that approved the protocol, according to the requirements of that METC.

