## 5. TREATMENT OF SUBJECTS

### ***5.1 Investigational product/treatment***

Before study inclusion, subjects will receive standard workup for the diagnosis SSD. This ENT workup includes a clinical history and interview, otologic examination, audiological testing and a MRI-scan for auditory nerve evaluation. Additionally, to determine eligibility for cochlear implantation, a CT-scan will be made to visualize the anatomy of the mastoid. When the diagnosis SSD is sure, all inclusion criteria are met and anatomy permits cochlear implantation, inclusion and randomisation will take place.

Subjects will be asked to read and sign the Informed Consent form presented by the patient's ENT-surgeon before randomisation. This physician will fill in a Demographics Form to gather subject information.

Baseline evaluation for gathering study related data will take place locally at randomisation:

- Pure tone audiometry
- Speech audiometry (CVC [consonant-vowel-consonant] score in quiet)
- Questionnaires: SSQ, HUI3, GBI, APHAB, TTO, VAS, EQ5D, HADS, and Tinnitus questionnaires.

The patients will be asked to fill in a monthly costs diary starting on the first day after inclusion until the end of the second year of the study. From then on, they will complete the costs diary once per 3 months.

For all patients in group A (CI group) and those in group B or C preferring BAHA implantation preoperative medical evaluation will be carried out locally by the anaesthesiologist and includes a determination of general health status and suitability for surgery. Subjects in the CI group will also be evaluated by the center's Cochlear Implant Team, as is standard care for cochlear implantees. The standard surgical procedures developed for placement of the BAHA and the internal components of the CI will be followed. Specific procedures for implanting of the devices will be left to the discretion of the surgeon.

The first evaluation visit will occur approximately 3 to 7 weeks after surgery in the CI group to custom fit the processor software. It will be programmed for optimal speech perception, based on individual subject preferences.

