In the BAHA and CROSS group patients will be evaluated after 6 and 12 weeks (see Figure 1). After finishing both test periods, the patient will be asked with which modality he or she wants to continue; either CROSS, BAHA or no treatment. When a patient chooses CROSS, he or she will be followed up by their own audiologist and returns to the UMC Utrecht for regular follow up sessions in this study. When a patient chooses a BAHA, a definitive BAHA will be implanted during an operation in the skull bone. Postoperative evaluation will take place according to regular BAHA-care procedures (e.g. mounting of abutment 6 weeks postoperatively when there is no skin reaction and software set up). Patients choosing no treatment will only be seen during the specified study follow up sessions.

In all treatment groups, standard evaluation sessions for collecting data will take place at 6, 12, 18 and 24 months after randomisation. After the first two years, subjects will be evaluated for data collection on yearly basis for three more years (36, 48 and 60 months). All objective evaluation measurements will take place at the UMC Utrecht to ensure that the data are gathered in an identical way. If considered necessary, extra sessions can exceptionally be added.

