### 6.2 Randomisation, blinding and treatment allocation

120 subjects will randomly be assigned to one of the three study groups: 30 in the CI group, 45 in the first-BAHA group and 45 in the first-CROSS group. A website randomisation

program, developed by the Julius Center, UMC Utrecht (<http://www.juliuscentrum.nl/random/>) shall be used to divide the subjects into the groups.

The randomisation chart is established before the start of the study by an independent data manager. When a local executor recruits a subject, the physician can log on to the site and enter the subject's characteristics. A block randomisation model will be used to make sure that the ratio CI:CROSS:BAHA subjects will be about equal ( $30:45:45 = 2:3:3$  per block). The physician will receive an allocation group number on his/her screen within a few seconds. It is only after the subject has signed the Informed Consent form that he/she is randomised and informed of the assigned group.

Logically, blinding is not possible since both patients and doctors will be able to see from the outside whether subjects have received a CI, BAHA or CROSS.

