#### Cost utility diary:

Subjects are asked to keep a monthly diary involving physical complaints and costs regarding general health and their hearing aid. After two years, the subjects will complete the cost utility diary once per three months. Also this questionnaire will address sick leave and other labor productivity related issues. The questionnaires are developed for this study in consultation with a specialist in Economics in Health Care, affiliated with the Julius Center for Health Sciences and Primary Care, UMC Utrecht. The outcomes of this questionnaire will represent the *numerator* of the cost utility ratio.

The questionnaires will be filled out by patients starting on the day of surgery in the CI group and in group B and C after patients made their definitive choice for BAHA, CROSS or no treatment. Subjects are asked to specify complaints and/or costs in the diary. All subjects will be reminded on regular basis by email to keep filling in the diary.

The HUI3 and EQ5D questionnaire outcomes will be plotted in a graph in which the area under the curve will reflect Quality Adjusted Life Years (QALYs). Also, these data will produce the *denominator* of the cost utility ratio.

The patient can choose if he/she would like to fill in the subjective questionnaires digitally or in a paper version. This will be verified in the Informed Consent Form. The patient is able to change his/her preference during the study period. All questionnaires that cannot be transformed to digital questionnaires (SSQ, VAS, TTO, EQ5D, Tinnitus Burden Questionnaire) will be filled out by all patients on paper.

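### Adverse events are captured only when volunteered or observed, so counts of non-specific symptoms may partly reflect how much contact each group has with the centre

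*Protocol*

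**What the plan says.** Section 7.2 defines an adverse event broadly, whether or not it is thought related to treatment, and then fixes how events are captured: "All adverse events reported spontaneously by the subject or observed by the investigator or his staff will be recorded". No routine question, checklist or adverse-event item at the study visits is stated.

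Section 6.2 explains why the trial is open: "Logically, blinding is not possible since both patients and doctors will be able to see from the outside" which device was received. It allocates "30 in the CI group, 45 in the first-BAHA group and 45 in the first-CROSS group".

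Contact is partly shared and partly not:

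- **Shared.** Section 5.1: "In all treatment groups, standard evaluation sessions for collecting data will take place at 6, 12, 18 and 24 months after randomisation". Yearly sessions follow at 36, 48 and 60 months.
- **Group A.** Patients have surgery, and then: "The first evaluation visit will occur approximately 3 to 7 weeks after surgery in the CI group to custom fit the processor software". Section 6.6 adds care by the CI team on top of the patient's own clinicians.
- **Groups B and C, early.** Section 5.1 has evaluations at 6 and 12 weeks.
- **BAHA choosers.** They have surgery and the usual postoperative BAHA care.
- **CROSS choosers.** Section 5.1 says of such a patient that "he or she will be followed up by their own audiologist and returns to the UMC Utrecht for regular follow up sessions in this study".
- **No treatment.** "Patients choosing no treatment will only be seen during the specified study follow up sessions".

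Section 6.3.2 also provides a diary: "Subjects are asked to keep a monthly diary involving physical complaints and costs regarding general health and their hearing aid". Its stated use is the numerator of the cost-utility ratio, and sections 7.2 and 7.3 do not mention it.

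**The concern.** A rule that depends on patients volunteering and staff noticing gives more recorded events where there are more occasions to volunteer and notice. Several events named in 7.2, such as dizziness, pain and uncomfortable loudness, are symptoms that staff often cannot see. Because nobody is blinded, patients and staff may also be readier to mention or record a symptom after implant surgery than after a choice of no treatment.

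Two things are at stake. First, a table of adverse events by group could show a difference in non-specific symptoms that comes partly from ascertainment. Second, symptoms that nobody volunteers may be under-recorded in any group. The protocol itself says in section 1.2 that patients with single-sided deafness have not so far been considered candidates for a CI, and in 9.3 that the evidence for benefit comes from low-quality studies. Section 7.1 obliges the investigator to act if the disadvantages prove greater than foreseen, which needs reliable capture. A symptom that was never asked about is hard to recover later.

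**Working it through.** The protocol gives no figure for adverse-event detection, so there is nothing to reproduce. The check is textual, followed by an illustration on labelled assumptions.

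**Step 1: who has sparse contact.** Section 4.4 forecasts 40 implanted BAHA, 30 CROSS and 20 no treatment among the 90 patients in groups B and C. CROSS and no-treatment patients come to the centre after their choice only for study sessions: 30 + 20 = 50 of 90. The 40 BAHA choosers have surgical follow-up, so their contact is closer to that of the 30 CI patients.

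**Step 2: what is shared.** All groups have visits at 6, 12, 18, 24, 36, 48 and 60 months, seven in all. These visits do not by themselves equalise capture, because the protocol states no adverse-event question at them. They are nevertheless the natural place for one.

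**Step 3: which events are exposed.** Implant failure and extrusion cannot occur in CROSS or no-treatment patients and are hard to miss in the others, so differential detection cannot create a false excess of them. Section 7.2 lists facial nerve stimulation and loudness complaints as specific to the CI, so they have no counterpart in controls. They can be under-recorded, but they cannot give a false contrast at equal risk. The exposed events are those that can arise in any group, such as dizziness and pain.

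**Step 4: illustration for such an event.** Assume the same true risk p in both arms, detection d_H under dense contact (CI and implanted BAHA) and d_L under sparse contact (CROSS and no treatment).

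- Recorded proportion, CI arm: p × d_H
- Recorded proportion, all controls: p × (40 × d_H + 50 × d_L) / 90
- Apparent ratio at equal true risk: d_H / [(40 × d_H + 50 × d_L) / 90]

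With p = 0.20, d_H = 0.80 and d_L = 0.40, the CI arm shows 0.20 × 0.80 = 16%. Sparse-contact controls show 0.20 × 0.40 = 8%. All controls show (40 × 0.16 + 50 × 0.08) / 90 = 10.4 / 90 = 11.6%. The ratio by randomised arm is 16 / 11.6 = 1.4.

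| Assumed d_H, d_L | Ratio, CI v the 50 sparse-contact controls | Mean detection, all 90 controls | Ratio, CI v all 90 controls |
|---|---|---|---|
| 0.9, 0.7 | 0.9/0.7 = 1.29 | (36 + 35)/90 = 0.789 | 1.14 |
| 0.9, 0.5 | 0.9/0.5 = 1.80 | (36 + 25)/90 = 0.678 | 1.33 |
| 0.8, 0.4 | 0.8/0.4 = 2.00 | (32 + 20)/90 = 0.578 | 1.38 |
| equal | 1.00 | equal | 1.00 |

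The ratios do not depend on p. The last row shows what equal ascertainment would achieve.

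**Step 5: can the diary fill the gap?** Section 5.1 starts it the day after inclusion in everyone. Section 6.3.2 starts it at surgery in group A and after the definitive choice in B and C, which follows two test periods (2 × 6 = 12 weeks). Under 6.3.2 it would cover group A from surgery but miss the B and C test periods, and so add a difference between groups. On the 5.1 schedule there are 24 monthly and 36/3 = 12 quarterly returns, or 36 per subject and 36 × 120 = 4,320 in all. Under 7.3 every adverse event found this way would have to be followed until it settles.

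**The case against.** The strongest reply is that no safety comparison exists to be biased. Safety is absent from the objectives (section 2), the endpoints (6.1) and the analysis (8). Section 9.3 is an advance ethical weighing of benefit and risk, and tabulation of adverse events may be left to a statistical analysis plan that is not shown. This stands. It limits the point to any between-group summary later made from these records, and to under-recording as such. It does not remove the point, because the capture rule itself is fixed in 7.2.

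Second, contact is not wholly unequal. The seven visits are common, B and C have early evaluations of their own, and the questionnaires put to everyone already cover pain, anxiety and depression, and tinnitus. This also stands and reduces the likely size. However, the protocol does not say that questionnaire answers enter the adverse-event record, and dizziness is not among the topics it lists for these instruments.

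Third, a reader might infer that a diary entry of dizziness is not an adverse event under the plan. The documents do not support this. Such an entry meets the definition in 7.2, and the protocol is merely silent on whether it is transferred to the adverse-event record.

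**Conclusion.** The point holds in a limited form. The rule in 7.2 is passive, the trial is open, and contact with the centre differs by treatment actually received. Counts of non-specific, subjective events may therefore partly reflect contact, and unvolunteered symptoms may be under-recorded. Device-bound events are largely unaffected.

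A reader might go further and conclude that adverse-event differences between CI and standard care would show contact instead of risk. That does not follow, because surgical and implant events are real treatment risks that controls without an implant cannot have.

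Nor should the illustration be read as a false doubling. The ratio of 2.00 compares the CI arm with 50 controls defined by a choice made after randomisation. By randomised arm the same assumptions give about 1.4, and the three assumed pairs give 1.14 to 1.38. These figures rest on assumed detection rates, on the section 4.4 forecast, and on BAHA choosers being detected like CI patients. They show a direction. The true size cannot be derived from the protocol.

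This is a worthwhile and inexpensive improvement. It does not threaten the primary result.

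**What to change.** In section 7.2, keep the present rule and add two provisions:

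1. At the visits common to all groups (6, 12, 18, 24, 36, 48 and 60 months), staff ask every subject the same open adverse-event question, followed by a short fixed checklist of the symptoms that 7.2 already names.
2. Adverse events are summarised by randomised group, with events solicited at these common visits shown separately from spontaneous or observed reports. The solicited events give the like-for-like view between groups, and the spontaneous reports keep early surgical and fitting events in the record.

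Do not rely on the diary for adverse-event capture unless its start dates in 5.1 and 6.3.2 are first reconciled so that it covers the same period in all groups.

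The cost is one short form and a few minutes at each existing visit, with no new visits and no change to treatment. The downside is more minor adverse events to record and to follow under 7.3. The open trial also remains open, so a standard question equalises the opportunity to report but not the patient's or the assessor's expectations.

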## **7.3 Follow up of serious adverse events**

In the case of implant failure, infection, extrusion or any other event resulting in the temporary non-use of the implant system, subjects will not be permanently excluded from the study, under the intention-to-treat-principle. Once the problem is solved, the subject will re-enter and continue the study for the amount of time left since he/she had not been operational with the device. A separate analysis for such a subject may be further conducted to control for possible biases.

All adverse events will be followed until they have abated, or until a stable situation has been reached. Depending on the event, follow up may require additional tests or medical procedures as indicated, and/or referral to the general physician or a medical specialist.

## **7.4 Monitoring**

This study will be monitored according to regulations by the UMC Utrecht and the Dutch government. The monitoring plan will be outlined in a separate document.

## **8. STATISTICAL ANALYSIS**

The aim of the study is to evaluate the clinical outcome after cochlear implantation, compared to BAHA, CROSS or unaided conditions, measured as speech perception in noise, sound localization, tinnitus and quality of life in patients with SSD. Also, a cost utility analysis will be performed (see section 6.3.2).

Overall, the study is an RCT, but subjects in group B and C run through the same two test periods within the first 3 months, afterwards they shall be treated with their modality of choice. As discussed previously, we expect 55% of patients in group B and C to choose for no treatment, we randomise more subjects in these groups (Desmet 2012). Thus equal comparison with the CI group will be possible during follow-up.

Major test intervals are the same in all study groups, namely 6, 12, 18, and 24 months after randomisation. After the first two years, subjects will be evaluated on yearly basis for three more years (36, 48 and 60 months).

The primary outcome will be the performance on the modified Plomp hearing test. The data are quantitative and will be presented as continuous variables. Between-group mean differences, rate differences and rate ratios with 96% confidence intervals will be calculated. Differences between the three groups will be analysed using the Kruskal Wallis test.

The secondary outcomes will be the performances on the other auditory tests and the questionnaires (see Section 6.3). Analyses of between-group differences will be performed with Chi-square-tests for categorical outcomes and Kruskal Wallis tests for continuous outcomes. Within-subject comparisons will entail differences of mean values. These will be analysed using paired t-tests for continuous measures.

Missing values will be imputed using multiple imputation and all analyses will be performed on an intention-to-treat basis.

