## **4.4 Sample size calculation**

To detect a clinically relevant difference of 5 dB SNR (standard deviation 5 dB) between the groups on the modified Plomp test, with an alpha of 0.05 and a power of 95%, 27 subjects

per group are needed. To be safe, a 10% margin is used to compensate for potential dropouts (e.g. non user cochlear implantees), resulting in 30 patients in the CI group. From recent literature we know that 55% of BAHA-on-headband users are not satisfied after their trial period and choose not to be implanted with a BAHA (Desmet 2012). Therefore, we must include more patients in groups B and C for compensation of the patients ending up in the 'no treatment' group. According to this proportion, 40 patients will end up with a BAHA. Patients not opting for a BAHA can choose for a CROSS. Based on many years of experience at our Audiologic Center, we expect ~60% to choose for CROSS. Thus, predicted numbers per group will be: CI (30), implanted BAHA (40), CROSS (30), 'no treatment' (20), leading to  $n = 45$  for groups B and C. These numbers allow for a valid calculation of the clinically relevant difference on the modified Plomp test.

Based on figures from the UMC Utrecht (in Dutch: Bedrijfsbureau DHS), approximately 25-30 patients per year with SSD present at the ENT outpatient department. Together with patients from the peripheral area of the UMC Utrecht, we expect the inclusion of patients to last for 3-4 years after the inclusion of the first patient. We also expect single-sided deaf patients from other areas of the country to present at the ENT department at the UMC Utrecht.

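### Groups B and C are sized, and declared comparable with the CI arm, by the device patients choose after randomisation, which contradicts the promised intention-to-treat analysis of the randomised groups

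*Protocol*

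**What the plan says.** Sections 3 and 6.2 of the protocol randomise 120 patients to A (CI, 30), B (BAHA then CROSS, 45) and C (CROSS then BAHA, 45). After two six-week test periods, patients in B and C choose an implanted BAHA, a CROSS or no treatment. The common follow-up visits start at 6 months, after that choice.

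Section 4.4 bases the calculation on "a clinically relevant difference of 5 dB SNR (standard deviation 5 dB) between the groups", "with an alpha of 0.05 and a power of 95%, 27 subjects" per group. It adds that "a 10% margin is used to compensate for potential dropouts (e.g. non user cochlear implantees), resulting in 30 patients in the CI group". It then enlarges B and C to compensate for patients who will end up untreated: "Thus, predicted numbers per group will be: CI (30), implanted BAHA (40), CROSS (30), 'no treatment' (20". It states that these numbers make the primary comparison valid.

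Section 8 gives the aim as CI against BAHA, CROSS or the unaided condition. It explains the larger B and C by the patients expected to choose nothing, and concludes: "Thus equal comparison with the CI group will be possible during follow-up". On the analysis it says: "Differences between the three groups will be analysed using the Kruskal Wallis test". It closes its analysis plan with "all analyses will be performed on an intention-to-treat basis".

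The objective in section 2 is CI against standard care with either CROSS or BAHA.

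**The concern.** Two groupings run through the plan. One is by randomised arm (A, B, C). The other is by what patients end up using (CI, BAHA, CROSS, nothing). The sample-size rationale and the comparability claim use the second. The test and the analysis principle point to the first.

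Randomisation protects only the first. Patients who keep a BAHA or CROSS do so after trying both, while CI patients pass through no such filter. Section 1.2 itself links the choice to the construct of the primary endpoint: among patients who reject current treatment, inadequate speech understanding in noise is given as the main reason in 45% of cases. Every modified Plomp result collected in B and C at follow-up comes after this sorting. If the chosen-device comparison were carried out on the strength of sections 4.4 and 8, its result would mix device effect with patient selection, yet it would be reported from a randomised trial.

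**Working it through.** **1. Reproducing the sample size.** Inputs from section 4.4: difference 5 dB, SD 5 dB, alpha 0.05 (two-sided assumed, as sidedness is not stated), power 95%. The standardised effect is 5/5 = 1.0. The two-sample t-test solution is n = 26.99, so 27 per group, as stated. A one-sided test would need 22 to 23 and does not fit. With the 10% margin, 27/0.9 = 30, as stated.

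**2. Reproducing the enlargement.** Inputs from section 4.4: 90 patients in B and C, 55% declining BAHA, about 60% of those taking CROSS.
- BAHA: 90 × 0.45 = 40.5
- CROSS: 90 × 0.55 × 0.6 = 29.7
- No treatment: 90 × 0.55 × 0.4 = 19.8

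These are the stated 40, 30 and 20, so the enlargement was built on chosen-device groups. Section 8 uses the 55% differently, as the share choosing no treatment. That would be 90 × 0.55 = 49.5 untreated rather than about 20.

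**3. Is the enlargement needed under intention-to-treat?** No. A patient who chooses nothing stays in the randomised arm and is analysed there. By step 1, 27 analysed per arm already give 95% power.

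**4. Power of the chosen-device contrasts** (5 dB, t-test, before dropout): CI 30 v BAHA 40, 98.3%; v CROSS 30, 96.8%; v no treatment 20, 92.4%. The last group is below 27 and the last power is below 95%. Good power would not in any case cure selection.

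**5. Power of the randomised contrast, A v B+C** (SD 5 dB, two-sided 0.05):
- 30 v 90: 99.7% for 5 dB
- after 10% loss, 27 v 81: 99.4% for 5 dB; the difference detectable with 95% power is 4.0 dB

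This takes 5 dB as the average difference over all of B and C. As a deliberately unfavourable variant, suppose the 22% untreated (20/90) did not differ from CI at all. The average difference is then 0.78 × 5 = 3.9 dB, with power 93.4% at 27 v 81.

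**6. What selection could do (illustration only).** Assume a normal outcome with SD 5 dB, and that the 45% choosing BAHA are the top 45% on a latent scale correlated r with the outcome. The mean of the top 45% of a standard normal is 0.880, so the shift is 0.880 × r × 5 dB:
- r = 0.2: 0.9 dB
- r = 0.3: 1.3 dB
- r = 0.5: 2.2 dB

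In simulation with no true effect (5,000 runs each, CI 30 v BAHA choosers 40), the comparison rejected at nominal 5% in about 12%, 20% and 47% of trials. A v B+C stayed at about 5%. The range of r is assumed; the documents give no value.

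**The case against.** The best defence is that the primary test is already randomised. Wherever the protocol counts three groups and says how they are formed (sections 1.1, 3 and 6.2), it means A, B and C, whereas the chosen-device scheme in section 4.4 has four. Read with the intention-to-treat sentence, the Kruskal-Wallis test is most naturally A v B v C. That stands, and it limits the point. Several stronger readings are tempting and are not supported:

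- *The main contrast is not randomised.* The text is contradictory on grouping; it does not prescribe a non-randomised primary test.
- *The trial cannot give a protected answer.* It can: A v B+C is in the design and well powered.
- *Untreated patients are dropped.* Section 4.4 lists them as a group, the aim in section 8 includes the unaided condition, and section 5.1 keeps them in follow-up.
- *The bias works against CI.* This is plausible if satisfied users keep their device, but patients with greater need might also be the ones to choose one. The documents do not settle the direction.
- *Reimbursement will rest on chosen-device contrasts.* Section 6.8 says "If this study shows BAHA or CROSS to be superior, reimbursement is already available in The Netherlands", but it names no contrast. It describes what patients may be offered afterwards and sets no decision rule.
- *The three-group test wastes substantial power.* At the 5 dB target, simulation with 27/40/41 gives about 98% for the three-group Kruskal-Wallis test and about 99% for a two-group rank test. The gap is larger at 3 dB (about 63% v 74%), but 3 dB is not the plan's target.

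The defence does not reach the sample-size rationale or the comparability sentence. Both rest on device choice and are at odds with intention-to-treat. This is not detail left to a statistical analysis plan, because the protocol states it as a property of the design.

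**Conclusion.** The point holds as a contradiction between two groupings together with one wrong claim. Sections 4.4 and 8 justify the size of B and C, and assert a fair comparison with CI, on the basis of groups that patients form themselves after randomisation. Section 8 also commits to intention-to-treat on groups defined elsewhere as randomised. Numbers in each device group do not confer comparability, and the stated reason for the enlargement disappears under intention-to-treat.

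The size of any resulting bias cannot be derived from the documents; the 0.9 to 2.2 dB figure depends wholly on the assumed correlation of 0.2 to 0.5. The contrast that fits the objective in section 2, the CI strategy against standard care with free choice of device, has 99.4% power for 5 dB at 27 v 81 (assuming SD 5 dB, a two-sided test, and 5 dB as the average over B and C). It is never named. A v B+C does not answer CI against BAHA or CI against CROSS separately. Nor does A v B or A v C, because after 12 weeks B and C follow the same policy and differ only in test sequence.

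**What to change.** In section 8:
- Name A versus B and C combined, as randomised and whatever device is chosen, as the primary comparison.
- State that the three groups are the randomised A, B and C.
- Label every comparison by chosen device (BAHA, CROSS, none) as non-randomised and supportive.
- Delete the sentence claiming that an equal comparison with CI follows from the larger B and C.

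In section 4.4, replace the device-choice rationale with one based on the randomised contrast, and present the 40/30/20 split as a forecast of uptake only. Reconcile the two meanings of the 55% in sections 4.4 and 8.

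The cost is wording: no extra patients or visits, and the planned 120 are enough. The real price is that claims against BAHA alone or CROSS alone become exploratory. The change should be made before outcome data are examined, since the choice of grouping can alter the result.
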